## Abstract

**Background:**

Chronic inguinodynia (groin pain) is a common complication following open inguinal hernia repair or a Pfannenstiel incision but may also be experienced after other types of (groin) surgery. If conservative treatments are to no avail, tailored remedial surgery, including a neurectomy and/or a (partial) meshectomy, may be considered. Retrospective studies in patients with chronic inguinodynia suggested that spinal anaesthesia is superior compared to general anaesthesia in terms of pain relief following remedial operations. This randomised controlled trial is designed to study the effect of type of anaesthesia (spinal or general) on pain relief following remedial surgery for inguinodynia.

**Methods:**

A total of 190 adult patients who suffer from unacceptable chronic (more than 3 months) inguinodynia, as subjectively judged by the patients themselves, are included. Only patients scheduled to undergo a neurectomy and/or a meshectomy by an open approach are considered for inclusion and randomised to spinal or general anaesthesia. Patients are excluded if pain is attributable to abdominal causes or if any contraindications for either type of anaesthesia are present. Primary outcome is effect of type of anaesthesia on pain relief. Secondary outcomes include patient satisfaction, quality of life, use of analgesics and (in)direct medical costs. Patient follow-up period is one year.

**Discussion:**

The first patient was included in January 2016. The expected trial deadline is December 2019. Potential effects are deemed related to the entire setting of type of anaesthesia. Since any setting is multifactorial, all of these factors may influence the outcome measures.

This is the first large randomised controlled trial comparing the two most frequently used anaesthetic techniques in remedial surgery for groin pain. There is a definite need for evidence-based strategies to optimise results of these types of surgery. Besides pain relief, other important patient-related outcome measures are assessed to include patient’s perspectives on outcome.

**Trial registration:**

The protocol (protocol number NL54115.015.15) is approved by the Medical Ethics Committee of Máxima Medical Centre, Veldhoven, The Netherlands. The study protocol was registered at www.trialregister.nl (NTR registration number: 5586) on 15 January 2016.

**Electronic supplementary material:**

The online version of this article (doi:10.1186/s13063-016-1746-x) contains supplementary material, which is available to authorized users.

## Background

### Background and objectives

Chronic postoperative groin pain (inguinodynia) is defined as pain beyond 3 months after inguinal surgery. In the majority of patients, inguinodynia develops following open inguinal hernia repair (66%; [name], [name], [name], [name], [name], [name] – unpublished observations). One third of patients with chronic postherniorrhaphy pain experience impairment of daily activities [1, 2]. This pain is either neuropathic (47–70%), nociceptive (26%) or a combination [3]. Inguinodynia may also be found after other types of groin surgery [4–7]. Concise history taking and an extensive physical examination provide the cornerstones for diagnosing inguinodynia. A diagnostic local nerve block may confirm the diagnosis [8, 9]. Interestingly, one of three patients benefits from these injections on the long term [10]. When these minimally invasive regimens fail, surgical options may be considered. Removal of the inguinal nerves, funiculolysis, and/or removal of the mesh may all be effective [7, 11–14, 17]. Furthermore, the post-Pfannenstiel pain syndrome, which often is neuropathic in origin, also responds well to an inguinal neurectomy [4].

The SolviMáx Centre of Excellence is a third-line referral centre for abdominal wall and groin pain. Experience with a spectrum of surgical procedures for inguinodynia is growing. One retrospective study in patients with inguinodynia suggested that spinal anaesthesia is associated with a superior outcome in terms of pain relief when compared to general anaesthesia [15]. A more robust trial is required to confirm these preliminary findings. The objective of the present paper is to present a randomised controlled trial that is designed to investigate the effect of type of anaesthesia on long-term pain relief in patients who are surgically treated for chronic inguinodynia.

## Methods

### Trial design

This monocenter, nonblinded, randomised controlled trial is performed in the SolviMáx Centre of Excellence for Abdominal Wall and Groin Pain. SolviMáx is a subdivision of the Surgical Department of Máxima Medical Center (MMC), a teaching hospital situated in the southern part of The Netherlands serving a population of approximately 200,000 inhabitants. The study aims at investigating a potential difference in pain relief following remedial surgery that is performed in two different settings, spinal anaesthesia versus general anaesthesia. The present trial is not considered a drug study as other variables associated with type of anaesthesia are not under control of the investigators. The present trial follows guidelines of the declaration of Helsinki (version 19 October 2013). The protocol (protocol number NL54115.015.15) is approved by the Medical Ethics Committee of Máxima Medical Centre, Veldhoven, the Netherlands. The study protocol (version 1) is registered at www.trialregister.nl (NTR registration number: 5586). The present paper is written according to the Standard Protocol Items: Recommendations for Interventional Trials (SPIRIT) 2013 Statement for reporting a clinical trial protocol [16]. The SPIRIT Checklist is provided as Additional file 1.

### Participants

Patient enrolment started in January 2016. Chronic inguinodynia that is unacceptable as subjectively judged by patients themselves is a prerequisite for inclusion. Only patients scheduled to undergo remedial surgery including a neurectomy and/or a meshectomy (if patients have mesh) by an open approach are considered for inclusion (Fig. 1). Patients are excluded if pain is due to intercostal neuralgia of the abdominal wall, such as abdominal cutaneous nerve entrapment syndrome (ACNES), or due to lateral femoral cutaneous nerve entrapment. Other contraindications are listed in Table 1. Cognitively impaired individuals, patients with ASA class IV or undergoing secondary or bilateral remedial surgery are also excluded.

**Fig. 1 Fig1:**
[figure not shown]
Mesh removal (*left*) and a neurectomy (*right*) in patients with inguinodynia following open inguinal hernia repair

**Table 1 Tab1:** Contraindications for spinal and general anaesthesia in the present trial

Relative contraindications	Absolute contraindications
*Spinal anaesthesia*	
Deformities of the spine^a^	Refusal by patient
Severe back pain or headache	Inadequate coagulation
	Pre-existent neurological deficiency
	Infection near puncture site
	Allergy to local anaesthetic
	Inability to communication properly
*General anaesthesia*	
Expected difficulty with airway	Refusal by patient
	Allergy for (components of) medications

^a^E.g. arthritis, osteoporosis, metastasis, spinal disc herniation, scoliosis

### Outcomes

Primary outcome is the effect of type of anaesthesia on pain relief after surgery. Patients are asked to score their pain using the Numerical Rating Scale (NRS, 0, absent pain – 10, worst pain imaginable). The first pain score is obtained in the preoperative phase (*t*
_0_), Fig. 2. Follow-up pain levels are determined at five time points to determine short-term (1 week, 6 weeks and 3 months postoperatively, *t*
_1–_
*t*
_3_) and long-term results (6 months and 12 months postoperatively, *t*
_4–_
*t*
_5_).

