### Statistical methods

Data analysis will be performed using SPSS version 22 (SPSS Inc. ^©^) for Windows. Digital data are easily exported from RM to SPSS. The primary outcome measure is pain relief using NRS as compared to the preoperative pain levels (*t*
_0_). Pain reduction is calculated by using the following formula:$$ PAINRELIEF=\left(1-\left(\mu NRS{t}_x/\mu NRS{t}_0\right)\right)\times 100 $$

Data of the general and spinal anaesthesia group will be compared using the Student’s *t* test or the Wilcoxon signed rank test, as appropriate.

Secondary outcome measures will be compared between groups at the various postoperative follow-up points. In addition, outcomes at each evaluation time (*t*
_1–_
*t*
_5_) will be compared to preoperative data within groups. The Student’s *t* test or the Wilcoxon signed rank test will be used as appropriate. *P* values ≤ 0.05 are considered statistically significant. Intention-to-treat analysis will be applied on the primary outcome measure.

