This is the first large randomised controlled trial comparing two routinely used anaesthetic techniques in remedial surgery for groin pain. There is a definite need for evidence-based strategies to optimise the results of these types of surgery. Besides pain relief, other patient-related outcome measures are assessed to include patient’s perspectives on outcome. The first study results are expected in 2019 and will be communicated via publication.

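### The primary outcome is pain relief at an unspecified visit: five follow-up times, one unadjusted 0.05 threshold, and no primary time point, although the objective is long-term relief

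*Protocol article*

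**What the plan says.** Under Outcomes the article states: "Primary outcome is the effect of type of anaesthesia on pain relief after surgery". No visit is named there or in the abstract. The same paragraph continues: "Follow-up pain levels are determined at five time points to determine short-term" results, meaning 1 week, 6 weeks and 3 months (t1 to t3), and "long-term results (6 months and 12 months postoperatively" (t4 and t5).

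Statistical methods repeats the definition, again without a visit: "The primary outcome measure is pain relief using NRS as compared to the preoperative pain levels". The formula expresses pain at t_x relative to pain at t0 as a percentage reduction, and x is not defined. For the group comparison it says "Data of the general and spinal anaesthesia group will be compared using the Student’s" t test or a Wilcoxon test. P values at or below 0.05 "are considered statistically significant". The article gives no adjustment, testing order or joint analysis over time.

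The only pointer to a time window is the objective in Background and objectives, which is "to investigate the effect of type of anaesthesia on long-term pain relief in patients who are surgically treated for chronic inguinodynia".

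Sample size rests on one pair of success rates, 77% with spinal and 58% with general anaesthesia. It gives no time point for them and arrives at 190 patients.

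**The concern.** A primary outcome needs a time point to be a single quantity. Here the variable, formula, test and threshold are all given, but the visit is left as a free index over five occasions from 1 week to 12 months. The objective narrows this to long-term relief, which still leaves two visits, and the outcome definition itself does not carry that restriction.

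Two things are at stake. First, the 5% error rate holds only if one comparison is the primary one. If the visit is chosen after the data are seen, or if any significant visit is accepted, the error rate is higher. Second, nothing in the text prevents a short-term difference from being reported as the primary result of a trial whose objective is long-term relief. The trial is unblinded with a patient-reported outcome, a limitation that the Discussion acknowledges, so a visit chosen afterwards would be hard to defend.

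**Working it through.** **1. The plan's own figure.** Inputs: success rates 0.77 and 0.58 (Sample size). Assumed because not stated: two-sided alpha 0.05, 80% power, 1:1 allocation, no continuity correction.

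n per arm = [1.96 × √(2 × p̄ × (1 − p̄)) + 0.8416 × √(p1(1 − p1) + p2(1 − p2))]² / (p1 − p2)²

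- p̄ = (0.77 + 0.58)/2 = 0.675, and 2 × 0.675 × 0.325 = 0.43875 (square root 0.6624)
- 0.77 × 0.23 + 0.58 × 0.42 = 0.4207 (square root 0.6486)
- n = (1.2982 + 0.5459)² / 0.19² = 3.4008 / 0.0361 = 94.2, rounded up to 95

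Total: 2 × 95 = 190, which reproduces the stated number. Power at 95 per arm is 80.3%. The trial is therefore sized for one comparison at the full 5%.

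**2. Error if any of several visits could count.** For k independent tests at 0.05 the chance of at least one false positive is 1 − 0.95^k:

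- k = 5: 1 − 0.95⁵ = 22.6%
- k = 2: 1 − 0.95² = 9.75%

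Repeated pain scores in the same patients are correlated, which lowers these figures. The article gives no correlations, so a range is assumed. The figures below are from simulation (2,000,000 multivariate normal draws, same correlation between all visits, two-sided critical value 1.96).

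| Assumed correlation | All five visits | 6 and 12 months only |
|---|---|---|
| 0 | 22.6% | 9.8% |
| 0.3 | 20.9% | 9.5% |
| 0.5 | 18.3% | 9.1% |
| 0.7 | 14.9% | 8.3% |
| 0.8 | 12.7% | 7.8% |
| 0.9 | 10.2% | 7.1% |

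With correlation that decays between successive visits (first-order autoregressive), the five-visit figures are 20.1% at 0.5, 17.1% at 0.7, 14.9% at 0.8 and 11.9% at 0.9. These lie within the same range.

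**3. What the alternatives cost.** One named visit tested at 5% leaves the error at 5% and power at 80.3% with 190 patients. If all five visits were kept as primary with a Bonferroni correction (0.05/5 = 0.01 each), power per comparison at 190 patients would fall to 58.9% for the same 77% against 58%. Restoring 80% would need 282 patients. Naming one visit is therefore the cheaper repair.

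**The case against.** The strongest reply is that the article does not plan five primary tests. A reader might infer this from t_x and the list of visits, but Statistical methods attaches its explicit visit-by-visit wording to the secondary outcomes and to the within-group comparisons with baseline. For the primary outcome it says only that the two groups will be compared. This stands: the defect is an open time point, not a stated programme of five primary tests. The error rates above are accordingly conditional on a rule that the article neither states nor excludes.

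It can also be said that the objective, read with the short-term and long-term labels, points away from early visits. This too has weight, and it is why the smaller range is given alongside the larger one. It does not settle the matter, since two visits remain and the outcome definition is not limited to them.

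Two further inferences are tempting and are not supported:

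- **An obvious 1-week advantage for spinal anaesthesia.** The Discussion cites benefits on postoperative pain and analgesic need in primary hernia repair, but gives no 1-week result. Interventions describes the spinal agent as relatively short-acting.
- **Publication before the 12-month data exist.** The Discussion says: "The first study results are expected in 2019 and will be communicated via publication". The abstract, however, gives December 2019 as the expected trial deadline. That agrees with about three years of accrual from January 2016 plus one year of follow-up. The accrual forecast is approximate, and the article does not announce a comparison of the arms before follow-up ends. At most the date is optimistic.

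Finally, an analysis plan that is not shown might name the visit. But the visit is part of what the primary outcome is. The article sets out the outcome, formula, test and threshold and leaves the index in the formula open, so this is more than detail left out of an article.

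**Conclusion.** The concern holds in this form: the primary outcome has no fixed time point, while the objective speaks of long-term relief and the sample size fits a single comparison. If significance at any eligible visit could count as the primary result, the false-positive risk would be about 8-10% when only 6 and 12 months are eligible (assumed correlations 0.3 to 0.8). It would be about 10-23% when all five visits are eligible (assumed correlations 0 to 0.9). Both ranges exceed 5%, and both rest on that any-visit rule and on correlations the article does not give. The absence of a named visit does not depend on either assumption.

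**What to change.** Before any analysis, name one long-term visit as the single primary time point and replace t_x in the primary definition with it. Twelve months fits the stated objective and the full follow-up. Six months is also labelled long-term, so the choice is the sponsor's, but it must be one visit. Test it once at two-sided 5%. Make the other four visits secondary and report them as between-arm estimates with 95% confidence intervals.

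Confirm that the 77% and 58% success rates apply at the chosen visit. If they come from another time, the basis for 190 patients has to be revisited. State that the primary comparison between arms is made only once follow-up to that visit is complete.

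The cost is that the other visits lose primary status. The trial is still recruiting, so the change is one of wording plus the check on the success rates, and it needs no extra patients if those rates are confirmed. A prespecified testing order, adjustment or joint model over visits would also control the error; a Bonferroni correction over five visits would lose power as shown above.

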**Fig. 2 Fig2:**
[figure not shown]
Content for the schedule of enrolment, interventions and assessments according to the SPIRIT Statement [16]

Secondary outcome measures are the effect of type of anaesthesia on quality of life and patient satisfaction. Quality of life is measured using the Short Form Health Survey-12 questionnaire (SF-12). To avoid confusion, satisfaction is also measured by a NRS-like method, using an 11-point rating scale.

Other secondary endpoints include differences in pain medication and both direct and indirect medical costs. Two different validated questionnaires, developed by the institute for Medical Technology Assessment (iMTA, Erasmus University Rotterdam, www.imta.nl) are used [18]. Complications (both surgery- and anaesthesia-related) are scored as based on the complication register of the Dutch Society for Anaesthesiologists. They are classified using the validated Clavien-Dindo classification [19]. Differences between various types of remedial surgery and specific causes of inguinodynia (primary inguinal hernia repair, primary Pfannenstiel incision, other index surgery, idiopathic inguinodynia) in relation to efficacy are also determined.

### Sample size

SolviMáx was founded in 2011. An increasing number of patients with potential abdominal wall or groin pain syndromes are referred to the surgical specialists (Fig. 3). Approximately 840 unique patients were analysed in 2014, and 1045 patients in 2015. Approximately 40–45% of these undergo remedial surgery.

**Fig. 3 Fig3:**
[figure not shown]
Number of unique patients analysed at SolviMáx Centre of Excellence for Chronic Abdominal Wall and Groin Pain over the years

Sample size was calculated by using a web-based calculator (www.openepi.com). Results from previous retrospective studies were used as criteria for eligibility were similar ([name], [name], [name], [name], [name], [name] – unpublished observations). Additional literature regarding anaesthesia on remedial surgery is not available. Previously demonstrated success rates were 77% in the spinal anaesthesia group and 58% in the general anaesthesia group ([name], [name], [name], [name], [name], [name] – unpublished observations). Based on these data, a sample size of 190 patients is calculated to demonstrate a potential effect of either type of anaesthesia on pain relief. This volume of patients is attained after three years as based on the number of included patients in previously performed studies (Fig. 4).

**Fig. 4 Fig4:**
[figure not shown]
Expected inclusion in the present trial, calculated by included patients in previously performed retrospective studies [15]

### Randomisation

Patients will be electronically randomised by the web-based research software Research Manager (RM, Cloud 9 Health Solutions^©^). No blocked randomisation or prestratification is performed. The decision to execute a neurectomy and/or mesh removal depends on patient history, physical examination and intraoperative findings [17]. Therefore, a prestratified randomisation is not possible for type of remedial surgery. Consequently, stratification will be executed within the analysis.

#### Sequence generation, allocation concealment and implementation

RM is used to establish an appropriate sequence generation and allocation concealment. RM generates a random allocation sequence, after which patients will be enrolled by the coordinating investigator. By using RM software, foreknowledge of (upcoming) anaesthesia assignments by the investigators is secured. Consequently, bias due to improper randomisation techniques is minimised.

### Blinding

Blinding of anaesthesiologists, surgeons and patients is not possible. Since the study is designed to investigate the setting of type of anaesthesia, where all factors associated with anaesthesia are of interest, blinding is not conditional for a robust conclusion on efficacy of either anaesthetic technique setting.

### Statistical methods

Data analysis will be performed using SPSS version 22 (SPSS Inc. ^©^) for Windows. Digital data are easily exported from RM to SPSS. The primary outcome measure is pain relief using NRS as compared to the preoperative pain levels (*t*
_0_). Pain reduction is calculated by using the following formula:$$ PAINRELIEF=\left(1-\left(\mu NRS{t}_x/\mu NRS{t}_0\right)\right)\times 100 $$

Data of the general and spinal anaesthesia group will be compared using the Student’s *t* test or the Wilcoxon signed rank test, as appropriate.

Secondary outcome measures will be compared between groups at the various postoperative follow-up points. In addition, outcomes at each evaluation time (*t*
_1–_
*t*
_5_) will be compared to preoperative data within groups. The Student’s *t* test or the Wilcoxon signed rank test will be used as appropriate. *P* values ≤ 0.05 are considered statistically significant. Intention-to-treat analysis will be applied on the primary outcome measure.

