In 2004, Burney and coauthors performed a randomised trial on the effects of anaesthesia in *primary* herniorrhaphy [26]. A disappointingly low recruitment rate was observed. The authors stated that patients had conceptualised concerns regarding the anaesthetic techniques, and consequently did not accept a random assignment [26]. It is theoretically possible that patients who are more anxious about the upcoming surgical procedure prefer general over spinal anaesthesia as they do not wish to experience any ‘noise’ from within the operation room. Studies have demonstrated that anxiety is a risk factor for postoperative pain [27–29]. When these patients are prone to more intense postoperative pain and thus prefer general anaesthesia, these issues may have influenced previous outcomes. In contrast, another study showed that preferred type of anaesthesia did not contribute to success after remedial surgery ([name], [name], [name], [name], [name], [name] – unpublished observations). In SolviMáx, a standard set of intake questionnaires is obtained from all preoperative patients including a Pain Catastrophising Scale (PCS) and a Hospital Anxiety and Depression Scale (HADS) [30–32]. By analysing these scores in relation to outcome, it is possible to analyse the influence of mental status in a later phase.

The majority of studies on chronic postoperative pain lack sufficient data to draw any robust conclusions. Previously, authors have claimed that extensive preoperative data, detailed characteristics of surgical procedures and measures of acute and chronic postoperative pain (up to 1 year) are essential for a proper evaluation of effects on pain [29]. The present trial design has included all of these factors and, therefore, the results can be considered of sufficient scientific evidence. Furthermore, cost-effectiveness of both anaesthetic techniques is assessed, which is critical for clinical practice.

A potential limitation of the present study is its nonblinded design. Blinding of patients is, in our opinion, unethical and hardly practicable. Moreover, the main outcomes of the present trial are subjective. Consequently, these outcomes may be contaminated by recall bias if patients enrolled in the trial are not blinded to their treatment allocation [33].

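### The primary pain-relief formula leaves μ undefined: as a group mean it cannot be put through the named tests, and as a patient's own score it is a percentage change unadjusted for baseline NRS

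*Protocol article*

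**What the plan says.** Under Outcomes, pain is measured on the 0 to 10 NRS. The baseline is collected: "The first pain score is obtained in the preoperative phase" (t0). Five follow-up scores come at 1 week, 6 weeks, and 3, 6 and 12 months, and the last two are labelled long-term.

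Under Statistical methods: "The primary outcome measure is pain relief using NRS as compared to the preoperative pain levels" (t0). Then "Pain reduction is calculated by using the following formula": PAINRELIEF = (1 − (μNRS t_x / μNRS t_0)) × 100. The symbol μ is not explained. The next sentence gives the test: "Data of the general and spinal anaesthesia group will be compared using the Student" t test or the Wilcoxon signed rank test, whichever suits.

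The article mentions no analysis of NRS adjusted for its baseline. The Randomisation section does promise stratification at the analysis stage, but in connection with the type of remedial surgery. Participants states no minimum NRS for entry: "Chronic inguinodynia that is unacceptable as subjectively judged by patients themselves is a prerequisite for inclusion".

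**The concern.** The formula and the test do not fit together as printed. In ordinary notation μ is a mean, and a ratio of two means is a single number for each arm and visit. A t test or rank test needs one value per patient.

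If μ is loose notation for the patient's own score, the tests can be run, but on another quantity. The trial is open label and the article itself calls its main outcomes subjective, so the primary outcome should not leave two readings that can point in opposite directions.

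The patient-level reading is also not the best use of the data. It uses t0 only as a divisor, so the score given to a drop of fixed size depends on where the patient started. The comparison between arms makes no adjustment for t0, although t0 NRS is planned for every patient.

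**Working it through.** **1. The plan's own figure.** The sample size of 190 rests on success rates of 77% and 58%. Power, sidedness and allocation ratio are not stated; 80%, two-sided 5% and 1:1 are assumed. With p̄ = 0.675:

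n = [1.96·√(2·0.675·0.325) + 0.8416·√(0.77·0.23 + 0.58·0.42)]² / 0.19² = (1.298 + 0.546)² / 0.0361 ≈ 94.2, so 95 per arm and 190 in total.

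The figure reproduces, with power 80.3% and no allowance for dropout. It is a two-proportion calculation, so it says nothing for or against the formula.

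**2. μ as a group mean.** Each arm yields one number per visit, with no spread between patients attached to it. Neither named test can take that as input.

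**3. The two readings can rank the arms differently.** Take two invented arms of two patients each, with baselines 10 and 4 in both:

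| | Follow-up | Ratio of means | Mean of patient percentages |
|---|---|---|---|
| Arm A | 2 and 4 | 1 − 3/7 = 57.1% | (80 + 0)/2 = 40.0% |
| Arm B | 5 and 2 | 1 − 3.5/7 = 50.0% | (50 + 50)/2 = 50.0% |

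Arm A looks better on the first reading and arm B on the second.

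**4. μ as the patient's score.** A 2-point drop counts as 25% from 8 to 6 and as 67% from 3 to 1. The scale is capped at +100% but can reach −900% (from 1 to 10), and it is undefined at a baseline of 0.

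**5. Power of percentage change against ANCOVA.** The documents give no NRS SD, correlation or effect in points, so every input here is an assumption:
- 95 per arm, two-sided 5%, 2,000 simulated trials per setting.
- Follow-up mean 3.5 in the control arm, SD 2.7, effect 1.1 points.
- Scores rounded and limited to 0–10, with baseline at least 1.

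Cells give power in % for a t test on percentage change v ANCOVA of follow-up NRS on t0. The Monte Carlo standard error of each figure is about √(0.8·0.2/2000) = 0.9 points.

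| Baseline mean, SD | Additive, r = 0.2 | Additive, r = 0.4 | Additive, r = 0.6 | Proportional effect |
|---|---|---|---|---|
| 7, 1.0 | 78.4 v 78.9 | 82.0 v 83.2 | 85.0 v 90.4 | 78.3 v 78.0 |
| 7, 1.5 | 76.1 v 77.0 | 81.9 v 84.6 | 86.6 v 91.2 | 76.6 v 75.8 |
| 7, 2.0 | 69.0 v 78.4 | 80.0 v 83.8 | 87.6 v 89.6 | 76.8 v 74.2 |
| 6, 2.0 | 62.6 v 78.0 | 76.4 v 83.6 | 86.8 v 90.1 | 75.2 v 71.6 |

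For an additive effect ANCOVA gains from 78.9 − 78.4 = 0.5 to 78.0 − 62.6 = 15.4 points. For an effect proportional to baseline it loses from 78.3 − 78.0 = 0.3 to 75.2 − 71.6 = 3.6 points.

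A two-sample rank test on the percentages narrows the additive gap to between 0.6 (76.4 v 77.0) and 6.6 points (83.8 v 90.4). The largest t-test gap becomes 73.6 v 78.0.

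**The case against.** The natural charitable reading is that values per patient were meant, because tests on patients follow at once, and that μ is careless notation. On that reading the first part is a request for clarification. This is fair, but the printed formula does not say so and it defines the primary outcome.

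Percentage pain relief is a legitimate endpoint, and an unadjusted comparison in a randomised trial is unbiased, with chance imbalance reflected in its standard error. Choice of covariates is often left to a SAP, which is not shown here. All of that stands. The point is not that adjustment is missing, but that the article fixes an ambiguous outcome and an unadjusted test where a better method needs no further data.

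A reader might infer more than the documents support:
- **That the outcome cannot be tested at all.** A ratio of group means can be tested from patient data by the delta method or a bootstrap. The article names neither.
- **That the plan necessarily loses power.** The loss depends on assumed inputs and on an additive effect. Proportional relief is the scale that the article itself chose, and there the advantage vanishes or reverses.
- **That patients with low baselines dominate the variance.** No entry floor is stated, but patients must have pain they find unacceptable and be scheduled for remedial surgery. With an assumed baseline mean of 6.5 and SD of 1.8, a rounded score of 2 or less has z = (2.5 − 6.5)/1.8 = −2.22, or about 1.3% of patients. Low denominators are possible but not shown to be common.
- **That the two faults add up.** The test problem belongs to the group-level reading. Unequal weighting and skewness belong to the patient-level reading. Only one of them can apply.

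**Conclusion.** The point holds in this limited form. As printed, the primary outcome formula and the named tests are incompatible if μ is a group mean. If μ is the patient's score, the outcome is a different quantity, an unadjusted percentage change. The article does not say which is meant, and the choice can reverse the ranking of the arms. This rests on the text and on arithmetic, not on assumed data.

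The case for baseline-adjusted NRS is sound, but its size is uncertain: about 0 to 15 percentage points of power for an additive effect, and nil to about 4 points the other way for a proportional one. Differences of a point or so are within simulation error. These ranges assume 95 per arm and the NRS means, SDs and correlations listed in the working, none of which the article supplies. The planned 190 is unaffected. The change is worth making before the data are analysed.

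**What to change.** 1. State that pain relief is computed for each patient from that patient's own scores, and drop or define μ. This is the minimum correction.
2. Make the primary comparison between arms an ANCOVA of the patient's NRS at a named long-term visit (for example 12 months) on arm, with t0 NRS as covariate. Report the adjusted difference with its 95% confidence interval.
3. Report percentage relief per patient, by arm and visit, as a descriptive summary.

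The cost is a change of wording and a standard model. The t0 and follow-up scores are already scheduled, and no visit or patient is added. The change is not wholly free: the primary effect is then a difference in NRS points rather than a percentage, and the sponsor should accept that openly. Adding the anxiety and catastrophising scores as covariates, or fitting a mixed model over all visits, is optional and not part of correcting the error.
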